## Results

Participant recruitment commenced in July 2023 and continued until August 2025. Follow-up data collection has commenced and will be completed by February 2026, with results expected in March 2026.

While the clinical trial study is ongoing, more than 75% of the target enrollment has been achieved. Preliminary data indicate that the intervention group is consistently outperforming the standard of care group in cancer screening adherence, supporting the study hypothesis that ASL-CHNs are effective in promoting cancer screening adherence among previously nonadherent participants who are DDBHH.

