**Results:**

As of August 2025, more than 75% of the target enrollment has been achieved. Preliminary data indicate that the intervention group is consistently outperforming the standard care group in cancer screening adherence, supporting the study hypothesis that ASL-CHNs are effective in promoting cancer screening adherence among previously nonadherent participants who are DDBHH.

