### Analysis Plan

All analyses will be conducted using SAS 9.4, with a 2-sided *P* value <.05 considered statistically significant. The DDBHH sample size sufficiently powers the detection of differences in the primary study outcomes. Based on a 2-sided Z-test with unpooled variance and a significance level (α) of .05, our study sample of 200 participants with 100 in each group will achieve at least 80% power to detect a difference in proportions of 14%-17% in the group proportions of adherence (ie, almost 82%-92% adherence in the intervention group, assuming 65%-78% of the eligible participants in the standard of care group have obtained age- and risk-appropriate cancer screening at follow-up) based on previous studies. Univariate statistics for baseline characteristics will be computed with stratification by group, as will patient-physician communication and cancer knowledge at baseline and follow-up. Bivariate analyses will examine group differences in patient characteristics. We will primarily use an “intent-to-treat” approach, using multivariable logistic regression to evaluate whether the recommended cancer screening rates are higher in the intervention group than in the standard of care group. Though we do not expect strong clustering effects with CHNs, we will account for potential clustering using generalized estimating equations, with regression models including group assignment and adjusting for relevant covariates.

If a sufficient number of participants cross over from the standard of care arm to the intervention group, we will conduct sensitivity analyses to assess whether they performed better than the standard of care group. Despite efforts to maximize retention, we anticipate approximately 25% attrition, which may introduce bias. To address this, we will determine if dropouts differ between randomized groups, adjust for any resulting imbalances in baseline covariate distributions, and perform sensitivity analyses under different assumptions (missing completely at random, participants who dropped out would have been responders, or participants who dropped out would have been nonresponders).

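### The article publishes which arm is ahead on the primary outcome while follow-up is still open, and describes neither an interim analysis nor a limit on who sees by-arm data

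*Protocol article*

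**What the plan says.** Results section: "Preliminary data indicate that the intervention group is consistently outperforming the standard of care group in cancer screening adherence". The sentence goes on to say that this supports the hypothesis that the navigators are effective. The Abstract repeats it almost word for word: "Preliminary data indicate that the intervention group is consistently outperforming the standard care group in cancer screening adherence". Neither place gives a rate, a denominator, a test or a date for the comparison.

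The same Results section says that the trial is ongoing, that over three quarters of target enrollment has been reached, that recruitment ran from July 2023 until August 2025, and that follow-up ends in February 2026. Screening adherence is the primary outcome (Outcome Measures), measured at closeout.

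The Analysis Plan sets the final test "with a 2-sided *P* value <.05 considered statistically significant". It describes no interim look. Nothing in the article restricts who may see outcome data by arm.

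Three safeguards are described. The Standard of Care Arm section says that participants stay blinded to their original assignment and that steps are taken against cross-contamination in a small community. Study Integrity tells navigators and participants to keep their participation confidential. Study Integrity also requires documentary proof of a completed screening.

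**The concern.** A comparison of arms on the primary outcome has been made, interpreted and put in print before the data are complete. Two things could follow.

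**Conduct of the remaining follow-up.** Blinding and non-discussion are meant to keep participants from learning which arm does better. A public statement that the navigator arm is ahead defeats part of that purpose. On the staff side, the Intervention Arm section has the navigator establish whether screening has occurred or is scheduled, while standard-care participants are asked to report back. No blinding of assessors is stated. Staff who know the trend may pursue contacts and documents unequally between arms. The plan already expects substantial loss ("we anticipate approximately 25% attrition"), so unequal effort could matter.

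**The final test.** If a look at the arms informed a decision about the trial, a final test at an unadjusted .05 no longer has a 5% error rate.

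**Working it through.** **1. The plan's own figure.** Inputs from the Analysis Plan: 100 per arm, unpooled Z-test, two-sided .05, and "almost 82%-92% adherence in the intervention group, assuming 65%-78% of the eligible participants in the standard of care group". Power = Φ(|p₁ − p₂| / √(p₁q₁/n + p₂q₂/n) − 1.96).

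- 65% vs 82%: SE = √(.65×.35/100 + .82×.18/100) = .0612; .17/.0612 = 2.776; Φ(0.816) = 79.3%.
- 78% vs 92%: SE = √(.78×.22/100 + .92×.08/100) = .0495; .14/.0495 = 2.827; Φ(0.867) = 80.7%.

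The stated 80% is reproduced to within a point. It is a single-analysis calculation with no allowance for a look.

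**2. A look with no decision attached.** If the comparison could not lead to an efficacy claim, early closure or a design change, only the final test counts and its error rate stays at 5%.

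**3. A look that could have ended the trial or supported a claim.** The information fraction t at the look is not given, so t = .50 to .75 is an assumption. The reported three quarters refers to enrollment. The outcome is measured at closeout, and intervention-arm support lasts 4 to 11 months, so information on outcomes lags behind enrollment. The look and final statistics are bivariate normal with correlation √t. Two-sided error with both tests at .05 is P(|Z_t| > 1.96 or |Z_1| > 1.96):

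| t | √t | Error |
|---|---|---|
| .50 | .707 | 8.3% |
| .60 | .775 | 8.0% |
| .75 | .866 | 7.3% |

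**4. The level that would restore 5%.** This uses O'Brien-Fleming-type spending with one look. The two-sided form spends 2[1 − Φ(1.96/√t)]; the form with .025 per tail spends 4[1 − Φ(2.241/√t)].

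| t | Spent by the look (two-sided / per tail) | Final level if continued to full information |
|---|---|---|
| .50 | .0056 / .0031 | .048 / .049 |
| .75 | .024 / .019 | .042 / .044 |

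The case matters. If the trial continued to full information after the look, the final level is about .042 to .049. If it in effect stopped near 75% of planned information, the level available is only what has been spent by then, about .019 to .024.

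**5. Cost in power if continued to full information.** At .042 (critical value 2.037): Φ(2.776 − 2.037) = 77.0% and Φ(2.827 − 2.037) = 78.5%. At .049 (critical value 1.969): 79.0% and 80.5%.

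**6. Recruitment dates.** The Abstract gives August 2025 as the date of the enrollment figure, and the Results section gives the same month as the end of recruitment. Setting and Participants plans at least 200 participants. No reason for the end of recruitment is given. The documents show that the two coincide, and nothing about cause.

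**The case against.** The strongest reply is that the statement is labelled preliminary, that the Conclusions and Discussion keep conditional wording, and that no interim test, P value or stopping decision is reported. Most of this stands, and it rules out several stronger readings that a reader might infer.

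- *The final P value is already invalid.* This is not supported. Keeping .05 is correct if nothing was decided on the look.
- *Recruitment was closed because of the trend.* This is not shown. The three-quarters figure is a lower bound, and Study Design says there have been no significant protocol modifications. That sentence does not, however, say whether by-arm data were in hand when recruitment ended.
- *There were repeated looks.* Four equally spaced unadjusted looks would give 12.6%, but no number of looks appears anywhere. The word used to describe the advantage could equally mean across screening types or strata.
- *Outcome assessment is open-label.* The article does not say so. Participants are described as blinded and proof of screening is required. What can be said is that no assessor blinding is stated. Nor does the article say which staff saw the data.
- *Covariates and imputation were left open to suit the trend.* Those rules may be fixed in an analysis plan that is not shown. The 4-to-11-month range is a rule about each participant's support, and the article does not present it as an analyst's choice.

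The published sentence itself remains. An unseen analysis plan cannot account for it, because the article makes the statement and draws the inference.

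**Conclusion.** The concern holds as a matter of trial conduct and reporting. By-arm primary-outcome data from an ongoing trial were interpreted as supporting the hypothesis, without figures, about six months before follow-up ends (August 2025 to February 2026). This weakens the participant blinding and contamination safeguards that the article relies on, and it exposes the remaining follow-up to unequal effort. Required documentation limits that risk but does not remove it. The size of any resulting bias cannot be estimated from the documents.

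The effect on type I error is conditional. It is nil if no decision used the look. It would be an increase to 8.3% or 7.3% if there was one unadjusted efficacy look at an assumed 50% or 75% of the information. The documents neither state nor exclude such a decision. This is a cheap improvement worth making while follow-up is open. It does not show that the final analysis is wrong.

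**What to change.** 1. Remove the by-arm effectiveness statement from the Abstract and the Results section. Enrollment progress can stay.
2. Withhold outcome data by arm from navigators, coordinators and investigators until database lock.
3. State when by-arm data were seen and by which roles, and whether the decision to close recruitment in August 2025 used them.
4. If it did, test the primary outcome at a spending-function level computed for the information actually available: about .042 to .049 if the trial went on to full information after one look at 50% to 75%, or about .019 to .024 if it stopped near 75%. If it did not, keep .05.
5. Label as post hoc any analysis rule fixed after the first look.

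The cost is less favourable wording and an access restriction. Only in the conditional case is there a stricter threshold. With continuation to full information, power would be about 77% to 79% for 65% vs 82%, and 79% to 80% for 78% vs 92%.

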## Discussion

### Anticipated Findings

The need to promote cancer screening adherence among adults who are DDBHH is significant. Our ASL-CHN intervention responds to the findings that individuals who are DDBHH face complex systemic, attitudinal, communication, and personal-level barriers when seeking cancer screening [1]. By using CHNs who are ASL-proficient and share lived experiences with the DDBHH community, the intervention addresses specific challenges identified in our needs assessment, including ineffective patient-physician communication, limited access to cancer information in ASL, misconceptions about medical procedures, difficulties navigating insurance systems, and intersectional barriers for individuals with multiple marginalized identities. The intervention focuses on training CHNs to provide appropriate support, clear explanations of cancer screening terminology using ASL, assistance with health care system navigation for cancer screenings, and emotional support—ultimately working to reduce cancer screening gaps documented among individuals who are DDBHH.

By engaging patients who are DDBHH via ASL-fluent navigators, the ASL-CHN intervention offers a scalable, participant-centered, and highly accessible solution. The language concordant communication included in ASL-CHN programming is intentionally designed to help participants focus on getting screened for cancer without feeling marginalized by the health care system. This careful approach is intended to mitigate health care mistrust, which is a major impediment to long-term engagement with preventive care in this population [13,14].

Preliminary evidence suggests that the ASL-CHN intervention is promising in promoting cancer screening and adherence among adults who are DDBHH [1]. The integration of personalized navigation with ASL-CHNs addresses key limitations of previous cancer screening interventions, which often lacked the accessible support necessary to sustain long-term health care engagement. Our approach in this randomized controlled trial aligns with recent studies that have highlighted the importance of combining Zoom and videophone technology with accessible human interaction to promote engagement and adherence in preventive health programs.

Understanding the mechanisms of action underlying the efficacy of ASL-CHN is highly significant. In this study, we are examining how our intervention improves cancer screening adherence through enhanced patient-centered care and strengthened shared decision-making between patients who are DDBHH and their physicians. By addressing communication barriers and empowering patients with accessible health information, ASL-CHN creates opportunities for meaningful dialogue about screening options, personal preferences, and concerns. These data will inform further refinement and optimization of the ASL-CHN program to maximize patient engagement in cancer prevention decisions.

This study has a few limitations worth acknowledging. We face retention challenges due to participants’ limited understanding of clinical trial processes and procedures. Additionally, our requirement for ASL fluency restricts our ability to include the broader DDBHH population who may use different communication methods. Our focus on only 5 major cancer screening types (breast, cervical, colorectal, lung, and prostate) may not address other important cancer prevention needs.

However, if successful in promoting cancer screening adherence for the 5 major cancer screening types, the ASL-CHN intervention could provide a practical, scalable option that health care providers can recommend to patients who are DDBHH who are not screening-adherent and may benefit from navigator support. Because early detection has been shown to reduce cancer mortality, the ASL-CHN intervention has the potential to play a critical role in improving health outcomes in this underserved population.

### Conclusions

The availability of an effective, accessible ASL-CHN service has the potential to shift future research that improves health outcomes, which helps lower the cost of associated health care and promote longer lives among people who are DDBHH who use ASL. We envision an ASL-CHN functioning as a patient navigator who is able to promote cancer screening adherence among people who are DDBHH. Patients who are DDBHH may experience even greater benefit from CHNs who are fluent in ASL, since so few clinicians are available and competent when caring for patients who are DDBHH. This should help support improvements in health care with regards to availability, affordability, adequacy, and administrative simplicity. It should also increase engagement with and adherence to cancer screenings, thereby improving health outcomes for people who are DDBHH who use ASL. To achieve this vision, cancer screening guidelines as well as navigation tools accessible in ASL are needed as resources for ASL-CHNs who encounter patients who are DDBHH in their care.

## Appendix

Multimedia Appendix 1 Peer review report by ZRG1 MOSS-*t* (54) Center for Scientific Review Special Emphasis Panel UNITE Transformative Research to Address Health Disparities and Advance Health Equity at Minority Serving Institutions (U01) (National Institutes of Health, USA).

## Abbreviations

ASL: American Sign Language
ASL-CHN: ASL-fluent community health navigator
CHN: community health navigator
CHW: community health worker
CONSORT: Consolidated Standards of Reporting Trials
DDBHH: deaf, deafblind, and hard of hearing
IRB: institutional review board
USPSTF: United States Preventive Services Task Force
